The rational to supplement acetylcholine in the treatment of post-ictal delirium is based on the hypothesis that changes in acetylcholine levels could be associated with cognitive side-effects of ECT (15). This may particularly involve older persons, considering changes in cholinergic signaling in the aging brain (16). Additionally, a lack of acetylcholine—the most important neurotransmitter of the cholinergic system—is thought to be one of the important causes of delirium in general (17). It is known that ECT initially causes an ictal peak of acetylcholine and postictal (e.g., post-ECT) drop of acetylcholine, mediated by cholinesterase (15, 18, 19). In 2015, van Schaik et al. published a case-series describing the putative beneficial effect of transdermal rivastigmine on ECT-induced cognitive side-effects in older ECT patients (8). Hence, a systematic review was done to examine the effect of (acetyl)cholinesterase inhibitors (AChI) (e.g., rivastigmine, donepezil, galantamine) to reduce cognitive side-effects of ECT (20). This systematic review by Henstra et al., included 5 clinical trials which all showed a positive effect of AChI on cognitive tests, but none of these studies studied the post-ECT delirium or inter-ictal delirium.

The primary objective of this study is to investigate in a multicenter, randomized, double-blind, placebo-controlled cross-over trial, whether rivastigmine can be used as a novel treatment to treat ECT-induced inter-ictal delirium in older persons. Additionally, we aim to investigate side-effects of rivastigmine, including its effects on ECT parameters and anesthesia-induced muscle relaxation. In order to detect persons with inter-ictal delirium who are eligible for the trial, longitudinal follow-up of persons treated with ECT is needed. Therefore, we embedded the trial in a cohort study. In this cohort study, comprehensive measurements of ECT-related cognitive side-effects—and their putative determinants—are done to gain insight into the broad palette of cognitive side-effects of ECT.

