### Exclusion criteria

Exclusion criteria for participation in the cohort study are comorbid somatic conditions that are a relative contraindication for ECT, according to the prevailing Dutch ECT-guidelines, e.g., recent (within 3 months) myocardial infarction or cerebrovascular accident, a diagnosis of neurocognitive disorder, insufficient command of the Dutch language and prior participation in the cohort study (27). Additional exclusion criteria for participation in the trial are: diagnosed (treatable) somatic causes of delirium other than ECT (e.g., urinary tract infection) and contra-indications for rivastigmine use, such as bradycardia or atrio-ventricular (AV) conduction disorder (first degree AV-block excluded), current use of a AChI or a known allergic or adverse reaction to rivastigmine. As it is a cross-over trial, each cross-over patient serves as his or her own control. Since large, intercurrent changes in individual patients' situation hamper a cross-over comparison, patients who switch from (right) unilateral electrode placement (RUL) to bilateral electrode placement (BL), or individuals who receive dose adjustments of antipsychotics during the trial will be marked as drop-outs. Notably, participation in the cohort can be continued when patients drop out due to trial specific exclusion criteria.

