
Furthermore, in order to investigate the safety and effect of rivastigmine on ECT-parameters and anesthesia, we measure blood pressure, peak heart rate, seizure length (EEG and motor duration in seconds), postictal suppression index (in %) and seizure threshold. Apart from the postictal suppression index and seizure length measured by the Thymatron IV (unavailable at sites with the spECTrum), all variables are recorded by a blinded anesthesiologist. Next, side-effects of rivastigmine are evaluated twice weekly (by a research assistant) using a four-point side-effects scale with the five most common side-effects of rivastigmine (nausea, vomiting, diarrhea, abdominal pain, allergic skin reaction), and an open question for additional side-effects.

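### The only heart-rate variable named for rivastigmine safety during ECT is the peak, which cannot show the lowest rate or a conduction event

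*Protocol article*

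**What the plan says.** The Introduction of the protocol article gives a secondary aim: "we aim to investigate side-effects of rivastigmine, including its effects on ECT parameters and anesthesia-induced muscle relaxation". Secondary outcome measures takes this up with a set of variables collected "in order to investigate the safety and effect of rivastigmine on ECT-parameters and anesthesia". The list reads "we measure blood pressure, peak heart rate, seizure length (EEG and motor duration in seconds", and continues with the postictal suppression index and seizure threshold. A blinded anesthesiologist records these, apart from the suppression index and seizure length that come from the Thymatron device. Table 1 shows the set as a single row, ECT characteristics, scheduled in the trial at T1, T2, T4 and T5.

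Under Exclusion criteria, patients are kept out of the trial for "contra-indications for rivastigmine use, such as bradycardia or atrio-ventricular (AV) conduction disorder (first degree AV-block excluded"; this is the only place where the article connects rivastigmine with a cardiac condition.

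Side-effects are also rated twice weekly on a scale covering "the five most common side-effects of rivastigmine (nausea, vomiting, diarrhea, abdominal pain, allergic skin reaction", together with "an open question for additional side-effects". The Harms section adds that adverse events in the trial are recorded whether the patient reports them or staff observe them.

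**The concern.** Both cardiac conditions that the article links to the drug concern slowing or conduction. The one heart-rate variable it names is a maximum. A safety question is answered best by a variable that moves when the foreseeable harm occurs, and the peak need not move when a patient has a slow phase or a block at another moment of the same session.

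The session is also where one would want to look. The section on treatment allocation, intervention and blinding gives a Tmax of 10 to 16 hours for the patch and has it applied the evening before ECT for that reason, so ECT is meant to fall near maximum exposure.

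At stake is how the safety results can be read. An unchanged peak heart rate could be taken as cardiac reassurance in older patients under anesthesia although the lowest rates had never been compared. The cross-over design would allow that comparison within patients, but only if the value is recorded.

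**Working it through.** The article gives no heart-rate mean, SD, threshold or expected frequency of bradycardia, so there is no stated figure to reproduce and no power to compute. The check sets the sections side by side.

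1. **What a maximum tells us.** Let M be the highest and m the lowest heart rate in a session. Knowing M gives only m ≤ M. Two sessions with equal M can have very different m, and a conduction event need not alter M at all. If rivastigmine lowers the whole rate profile, M may fall as well, and a paired comparison of M could detect that. The peak is therefore an incomplete measure of slowing, not an uninformative one.

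2. **What each planned route can capture.**

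| Route | Section | Lowest rate or conduction event? |
|---|---|---|
| Peak heart rate | Secondary outcome measures | No, only a lowered peak |
| Blood pressure | Secondary outcome measures | Neither rate nor conduction |
| Five-item side-effect scale | Secondary outcome measures | No; four gastrointestinal items and one skin item |
| Open side-effect question | Secondary outcome measures | Possible, unstructured |
| Assessment before each ECT session | Treatment allocation, intervention, and blinding | Possible, if reported |
| Reported or staff-observed adverse events, serious adverse events | Harms | Possible, if someone judges it an event |
| ECG during the trial | Table 1 | No such row |

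3. **How well the unstructured routes work for this event.** During the session the patient is anesthetized and given a muscle relaxant (ECT procedure), and entered the trial because of a positive CAM or an MMSE drop of at least 4 points (Study population and inclusion criteria). Self-report of a slow phase under anesthesia is implausible. Staff observation remains, but the article gives no rate or rhythm criterion for calling slowing an event, so capture may differ between observers in the four centers.

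4. **How many records are involved.** Data analysis gives two ECT sessions per treatment period, and Table 1 agrees (T1 and T2, then T4 and T5). With the planned 30 completers, 30 × 2 = 60 sessions on each treatment. The section on treatment allocation says that an arm lasts four consecutive sessions; if that means one period and not the whole sequence, the count is 30 × 4 = 120. This is a count of records without a named lowest-rate value, not an effect size, and the argument does not depend on which number is right.

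5. **What is not affected.** The primary outcome is the change in DRS-R-98. No heart-rate variable enters it, the sample size calculation or the significance level.

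**The case against.** A reader might infer that the protocol measures its safety question in the wrong direction. The article does not support that. It never calls peak heart rate its cardiac safety measure, and it never poses bradycardia as a safety hypothesis: bradycardia and AV conduction disorder appear only as contra-indications, and are handled by exclusion. Peak heart rate is a reasonable ECT parameter, which is part of the stated purpose, and a fall in the peak would be detectable.

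A reader might also infer that slowing would be found only if the patient volunteered it. That is wrong too. The open question, the assessment before every session and the recording of staff-observed events all exist, and they run in both blinded periods, so events that are noticed can be tabulated by treatment.

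Finally, the source is a condensed article. Table 1 does not itemise ECT characteristics, so the case report form may already hold a resting or lowest rate or rhythm notes. It cannot be claimed that no session record contains such a value.

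All of this stands, and it reduces the point considerably. It does not remove it. The article does not merely say heart rate and leave the detail elsewhere; it names the peak, which is a stated choice of variable. The other routes are real, but none yields a quantitative value per session that can be compared between rivastigmine and placebo within the same patient.

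**Conclusion.** The point holds in a limited form. As listed, the variables for rivastigmine safety at ECT can show a lowered peak heart rate, but not the lowest rate or a conduction event, although slowing and conduction are the only cardiac problems the article associates with the drug. Slowing would be picked up through unstructured reporting alone, without a paired quantitative comparison.

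Severity is low, because this concerns the completeness of one secondary safety measure. Confidence is moderate, because the conclusion assumes that the article's list is the full list of heart-rate variables, and the case report form behind the ECT characteristics row is not available to check. The absence of a separate safety board (Monitoring and auditing) does not bear on which variable is recorded and is not part of the argument.

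**What to change.** In the ECT-characteristics record at T1, T2, T4 and T5, add two fields: the lowest heart rate, and any observed rhythm or conduction event. Both should cover the session as monitored by the anesthesiologist and be entered by the same blinded anesthesiologist. The window should stop there, because the article does not place the anesthesiologist in recovery; the reorientation assessment of up to 90 minutes after ECT is done by the research nurse.

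Name the lowest heart rate as the quantity compared within patients between the rivastigmine and placebo periods, report rhythm and conduction events by treatment, and keep peak heart rate as a measure of the seizure response. If the full protocol already records these items, no new data are needed; it is enough to list them as the safety comparison.

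The cost is a minor eCRF change, and sessions already completed will lack the data. This alters what is recorded and compared, not how patients are treated.

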#### Patient characteristics

In addition to the outcome measures, various patient characteristics are assessed, including socio-demographics, physical-, clinical-, and neurocognitive characteristics. All variables are collected by a trained research nurse or assistant, unless otherwise specified.

Socio-demographics include age, gender, partner status, current living situation, level of education (total years of education), all self-reported.

Physical characteristics include Body Mass Index (BMI), waist circumference (centimeters), blood pressure (mmHg), vision- and hearing, dental condition, smoking status (current, former, never), alcohol use (number of drinks per week), activities of daily living, physical activity, International Physical Activity Questionnaire (38), Short Physical Performance Battery (39) and frailty status (40). Vision and hearing ability is measured with self-reported questions on the quality of vision and hearing and questions on the presence of glasses or hearing devices. Dental condition is measured with a question on the presence of dentures. Level of activities of daily living (ADL) is measured through 6 questions on the ability of the patient to (1) shower, (2) dress up, (3) go to the bathroom, (4) transfer from bed to chair, (5) eat, and whether the patient (6) uses incontinence material. Physical activity is measured by a 16-item questionnaire on self-reported mobility (i.e., questions on the risk of falls, need of walking aids, maximum walking distance, ability to climb stairs, cycling) (available upon request). The International Physical Activity Questionnaire (IPAQ) is a validated questionnaire in older adults for assessing physical activity, measured in metabolic equivalent minutes (MET-minutes). The MET-minutes are calculated through assigning a ratio of energy expenditure during an activity (as compared to energy expenditure in resting state), multiplied by the amount of minutes these activities are performed per week (38). The Short Physical Performance Battery (SPPB) is a reliable and valid score to assess lower extremity function. The SPPB sums up the scores of three timed performance tests: the tandem balance test; the walking speed; and the repeated rising up from the chair-test. It gives important information on actual lower extremity function and is a predictor and outcome which can be used for physical decline (41). The prevalence of frailty using Fried's phenotype will be assessed (40). This phenotype consists of 5 variables: unintentional weight loss, muscle weakness, self-reported exhaustion, poor endurance, and low activity level. Patients will be classified as non-frail (0 variables present), pre-frail (1-2 variables present) or frail (3 or more variables present). Unintentional weight loss is measured with a positive response to the CIDI question about unwanted weight loss (with a minimum of 1 kg/week or a BMI ≤ 18.5 kg/m^2^). Muscle weakness is measured through hand grip strength [for a detailed description see Penninx et al. (42)]. Self-reported exhaustion is measured according to two statements of the Center for Epidemiologic Studies-Depression scale (43) (CES-D), namely (a) I felt that everything I did was an effort, and (b) I could not get going. If at least one condition is present for 3 days or more during the last week, the criterion is positive. Poor endurance will be defined with the walking speed test from the SPPB. Low physical activity level will be defined with the IPAQ.

Clinical characteristics include somatic and psychiatric (family) history, presence of chronic diseases, medication use, treatment resistance, Geriatric Depression Scale (44), Montgomery Åsberg Depression Rating Scale (28), Beck Anxiety Index (45), Apathy Evaluation Scale (46), and the CORE (47). Somatic and psychiatric (family) history is self-reported and checked by examining clinical records. Standardized questions for chronic diseases are used, which include chronic pulmonary disease, cardiovascular disease, diabetes, cerebrovascular disease, osteoarthritis, rheumatoid arthritis and cancer. These categories were chosen based on prevalence rates (48). In addition, patients are asked whether they have any other chronic diseases (defined as a disease of which symptoms and/or treatment had been present for at least 3 months). Current medication use, medication changes during ECT course and treatment resistance through the Antidepressant Treatment History Form: Short Form (49) (ATHF-SF) are noted by the treating physician. The 15-item self-reported Geriatric Depression Scale (GDS) is a valid and reliable scale for differentiating depressed from non-depressed patients (44). The 10-item Montgomery Åsberg Depression Rating Scale (MADRS) is a widely used scale to measure the severity of depressive symptoms with high interrater reliability and good validity (50). The 21-item Beck Anxiety Index (BAI) helps to discriminate between anxiety and depression and measures the severity of anxiety with high internal consistency and test-retest reliability (45). Apathy is measured with the Apathy Evaluation Scale—clinician version (46) (AES-C). The AES-C is a well-known scale with good reliability and validity (46). Severity of psychomotor symptoms and the probability of melancholia is measured by the CORE, an 18-item observation scale subdivided into three subscales (retardation, agitation and non-interaction) (47). It has high inter-rater reliability and good validity for psychomotor disturbance in depressed persons (51).

Neurocognitive characteristics include the Stroop Color and Word Test (52), the 15-words Test (53), the Trail Making Test (54), Kopelman Autobiographical Memory Interview (55), the Visual Association Test (56), self-reported cognitive decline and the Informant Questionnaire on Cognitive Decline in the Elderly- Short Form (57) (IQCODE-SF). The Stroop Color and Word Test is a neuropsychological test extensively used to assess the ability to inhibit cognitive interference, working memory and speed of visual search (58). The 15-words test, or Auditory Verbal Learning Test, is a test used to assess attention, memory, and learning ability. The Trail Making Test A and B is used to assess executive functioning, visual search and scanning and speed of processing. Kopelman Autobiographical Memory Interview is used to measure autobiographical and semantic memory. The Visual Association Test is used to measure signs of anterograde amnesia through visual associated learning. Self-reported decline is measured with the CIDI questionnaire, section E (22). The IQCODE-SF is a 16-item questionnaire for caregivers that is used for screening and evaluation of cognitive decline and dementia in patients.

In a subset of patients—those derived from GGZ inGeest and OLVG hospital and whom provided informed consent– we conduct an electroencephalogram (EEG) and (Functional) Magnetic Resonance Imaging [(f)MRI] at baseline. EEG assessment is a non-invasive, widely available, cheap and objective measure for brain functioning, capable of detecting signs of delirium or vulnerability of the brain associated with neurocognitive disorder (59, 60). On MRI, the presence of white matter hyperintensities [Fazekas score (61)], cortical atrophy [Pasquier or GCA score (62)] and medial temporal lobe atrophy [Scheltens or MTA score (63)] atrophy are rated. In order to obtain insight in brain activity as well, MRI scans will be extended by 15–20 min to derive functional imaging (fMRI).

Laboratory characteristics include inflammation markers (e.g., high sensitive CRP, interleukin-6), s100-beta, the regular laboratory tests done in a comprehensive geriatric assessment (such as complete blood count, basic electrolyte and metabolic panel, kidney and thyroid functioning, vitamin and lipid status) and urine samples (64, 65). S100-beta is a calcium-binding protein expressed by astrocytes, associated with delirious states and cognitive decline during ECT (66, 67). Urine morning samples are collected for the assessment of several biomarkers which have shown to be involved in the prediction, diagnosis and evaluation of antidepressant treatment in recent studies (68, 69). The final selection of biomarkers of interest will be done at time of laboratory processing, depending on state-of-the art laboratory techniques, possibly including additional inflammation markers and/or neurotransmitters.

### Sample size calculation

We estimated that in our vulnerable study population, prevalence rates of delirium and profound cognitive decline are ~20%, based on a previous study (11). In order to detect a reduction on the DRS-R-98 of 4 points (SD ± 7), at 80% power with α = 0.05, 120 delirious patients should be included in a non-cross-over trial. These patients (*n* = 120) should be identified during regular ECT (cohort study). Since the estimated prevalence of inter-ictal delirium is ~20%, the cohort should include in total at least 600–1,000 persons in order to select 120 patients. This is not possible, due to limited availability of resources. Therefore, a cross-over design will be used. A cross-over design requires fewer patients than a non-cross-over trial to achieve similar power. With an estimated correlation between intra-individual measurements of *r* = 0.50, a cross-over trial requires only 25% of the number of patients (70). Hence, a total of 30 patients provide sufficient power for the trial. With an estimated dropout of 20%, 38 patients need to be included to obtain sufficient power for the trial. We aimed at a probability of 75% to include 38 delirious patients in the trial, which would amount to 210 patients in the cohort. Eventually, with an additional 20% margin of safety due to estimated prevalence, we decided to set the inclusion goal at 250 patients for the cohort, to achieve a sample of 30 delirious patients completing the trial. However, during the first months of data-collection, the prevalence of inter-ictal delirium was noticeably higher, namely ~25%. Hence, in an amendment, the goal of inclusion in the cohort was set back to 150 patients.

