#### Data analysis

Significance will be set at *p* < 0.05 for all statistics and 95% confidence intervals will be presented. Intention to treat analyses will be conducted. Descriptive baseline statistics will be generated for the patients included in the trial. As the trial is a patient cross-over design, no comparison or correction for baseline variables will be done.

To estimate the efficacy of rivastigmine on inter-ictal delirium in the RECALL trial, delta scores of the DRS-R-98 will be used. These delta scores will be computed over the period of rivastigmine (intervention, 2 ECT sessions, 7 days) and placebo (comparison, 2 ECT sessions, 7 days) separately. For further details, see section Primary outcome measure. Analysis of Variance (ANOVA) by a mixed model for repeated measures, with treatment (rivastigmine vs. placebo) as a within effect and sequence of treatment (arm A vs. arm B) as a between factor, will be performed. Additionally, the association between rivastigmine and (delta-scores of the) DRS-R-98 will be examined in a traditional regression model, with putative effect modifiers, confounders and determinants.

Cox's regression analyses will be conducted in the RECALL cohort, with outcome defined as the (time to) occurrence of inter-ictal delirium measured by a positive CAM and/or a decline of MMSE of 4 points, adjusted for putative effect modifiers, confounders and determinants. Additionally, putative patterns of cognitive decline will be identified by data-driven methods (e.g., latent-class analysis), based on cognitive outcome measures. Future analyses in the data will depend on appropriate research questions.

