The cross-over design is chosen for three specific reasons; (1) to reduce the influence of confounding covariates, as each crossover patient serves as his or her own control; (2) to enable all trial patients to benefit from the study medication; and (3) most important, feasibility, as cross-over designs require fewer patients than non-cross-over designs to achieve sufficient power (71). The feasibility was the major argument for the design team as this is a population that is particularly hard to study. It is difficult to include patients due to less motivation which is a symptom of their disease, and—in case of legal incapability- doubts from the legal representative (e.g., family) to agree to an additional extensive battery of tests during the treatment. In addition, as in all studies on depression, we predict that the anhedonia and indecisiveness, core symptoms of depression, cause difficulties for patients to stay motivated during the entire study, resulting in missing data. The cross-over design allows this study to achieve sufficient power with 30 delirious patients completing the trial. A potential bias in cross-over designs may be “carry-over” effects. However, rivastigmine has a short elimination time [T1/2 patch = 3.4 h (72)], therefore a minimal “wash-out” period of 1 day is deemed sufficient. After removal of the patch, rivastigmine is eliminated for more than 99% within 24 h—or before the next ECT session is done. Furthermore, transdermal rivastigmine was chosen over other AChI due to reported superiority on gastro-intestinal side-effects and similar expected efficacy (73–75).

A limitation of our study is the possibly invalid use of the MMSE as an inclusion measure for patients with an inter-ictal delirium. It might be improper, as it is previously not validated as a tool for the diagnosis of inter-ictal delirium, or any other delirium (76). The same goes for the MMSE as a measure of delirium severity. However, we claim, based on our clinical experience, that inter-ictal delirium does not always behave as a “regular” delirium and therefore does not always meet the criteria for delirium as measured with the CAM. For example, hallucinations are often lacking, and the patients usually suffer from clouding of consciousness, persistent disorientation or reduced speed of processing. Hence, by screening for inter-ictal delirium using the CAM only, eligible patients for the trial might be missed.

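### The 30-completer target takes 25% of 120, but the stated inputs do not give 120, and the 25% factor does not fit delta scores that share T3

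*Protocol article*

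**What the plan says.** The section 'Sample size calculation' aims to detect a "reduction on the DRS-R-98 of 4 points (SD ± 7") and states that "at 80% power with α = 0.05, 120 delirious patients should be included in a non-cross-over trial". It then invokes an "estimated correlation between intra-individual measurements of *r* = 0.50" and concludes that "a cross-over trial requires only 25% of the number of patients", hence 30. A 20% dropout allowance raises 30 to 38, and the cohort target is built on those figures. The Discussion repeats the claim: "The cross-over design allows this study to achieve sufficient power with 30 delirious patients completing the trial".

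The analysed quantity is set elsewhere. 'Primary outcome measure' and 'Data analysis' compare DRS-R-98 delta scores between the rivastigmine and placebo periods, namely T3−T0 and T6−T3. The model is a mixed-model ANOVA with treatment within patients and sequence between patients. T3 is thus the end of period 1 and also the starting value of period 2.

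The sample size section does not say whether SD 7 and r = 0.50 describe single scores or delta scores.

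**The concern.** Two links in the chain from 120 to 30 look wrong. The parallel-group figure is larger than its own inputs give. The cross-over saving of 75% is the saving for comparing one score per period, whereas the planned comparison is between two changes with a common middle measurement. That shared measurement pushes the correlation between the two changes below zero, and a negative correlation reduces the saving.

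The first discrepancy errs on the safe side. The second works the other way and is potentially much larger. At stake is the claim that 30 completers are enough for the primary comparison. No interim analysis is planned, so a shortfall would show only at the end, when a null result might be read as evidence against the drug rather than as low power.

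**Working it through.** **Inputs.** From 'Sample size calculation': difference 4, SD 7, α = 0.05, power 80%, r = 0.50, factor 25%, 30 completers, dropout 20%. Sidedness is not stated; two-sided is assumed, in keeping with the 95% confidence intervals in 'Data analysis'. Equal allocation is assumed for the parallel comparator.

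**The plan's own chain.** (1 − 0.50)/2 = 0.25; 0.25 × 120 = 30; 30/0.8 = 37.5, rounded up to 38. These steps reproduce. The 120 does not.

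**Parallel-group size.** Per arm, n = 2 × [7 × (1.960 + 0.842)/4]² = 48.1, so 49 per arm and 98 in total. The two-sample t-test gives 79.96% power at 98, 80.8% at 100 and 87.4% at 120. Other settings do not give 120 either: one-sided 80% gives 76, two-sided 85% gives 110, two-sided 90% gives 130.

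**What the 25% factor requires.** The ratio of cross-over to parallel size is (1 − ρ)/2, where ρ is the correlation between the two values compared within a patient. A ratio of 25% needs ρ = +0.5.

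**Correlation of the planned deltas.** With equal variances, r1 the correlation between adjacent visits and r2 that between T0 and T6:

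Corr(T3−T0, T6−T3) = (2·r1 − 1 − r2)/(2 − 2·r1)

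- Equal correlations, r1 = r2 = 0.5: (1 − 1 − 0.5)/1 = −0.5. Under equal correlations the result is −0.5 for any r.
- Decay with lag (AR(1), an assumption), r1 = 0.5, r2 = 0.25: (1 − 1 − 0.25)/1 = −0.25. In general it is −(1 − r)/2.
- To reach +0.5 with r1 = 0.5, r2 would have to be −0.5, which is not plausible.

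The factor becomes (1 + 0.5)/2 = 75% or (1 + 0.25)/2 = 62.5%.

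**SD of the within-patient contrast.** If single scores have SD 7 and adjacent visits correlate at 0.5, each delta has SD 7 × √(2 × 0.5) = 7, so SD 7 applies on either reading. The difference between the two deltas has SD 7 × √(2(1 − ρ)): 12.12 for ρ = −0.5 and 11.07 for ρ = −0.25. For T3 versus T6 at correlation 0.5 it is 7.0.

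**Which effect the deltas see.** If 4 points is a difference between deltas, the contrast is 4. If it is a score effect that disappears fully after the switch, the rivastigmine-first sequence shows −4 then +4 (contrast 8), and the placebo-first sequence shows 0 then −4 (contrast 4). The average is 6.

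**Power** (noncentral t, N − 2 degrees of freedom):

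| Analysis and reading | Effect | SD of contrast | Power at 30 | Completers for 80% |
|---|---|---|---|---|
| Deltas, 4 points on delta scale, equal correlations | 4 | 12.12 | 41.5% | 75 |
| Same, decaying correlation | 4 | 11.07 | 48.1% | 63 |
| Deltas, reversible 4-point score effect, equal correlations | 6 | 12.12 | 74.4% | 35 |
| Same, decaying correlation | 6 | 11.07 | 81.8% | 29 |
| T3 versus T6, reversible 4-point score effect | 4 | 7.0 | 85.6% | 27 |

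**The case against.** The best defence is that the 4 points and SD 7 read most naturally as describing scores, and that the Discussion argues carry-over is minimal, which fits a reversible effect. Power for the planned analysis is then 74% to 82%: a modest shortfall or none. This stands, and it is why the point cannot be that the trial is shown to be underpowered.

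Three stronger readings are tempting, and the document does not support them.

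- **That 80% power is simply false.** The range runs from 41.5% to 82%, and the text does not settle which end applies.
- **That changing the analysis would lift power from 41.5% to 86%.** Those figures assume different true effects. A delta contrast of 4 corresponds either to a reversible score effect of 4/1.5 = 2.67 points, where T3 versus T6 has 52% power at 30 completers, or to a 4-point effect that persists after the switch. In the second case T3 versus T6 averages (0 + 4)/2 = 2 points and has 33% power, less than the deltas have.
- **That dropout is counted twice.** 100 × 1.2 and 96/0.8 both equal 120, so an allowance may be hidden there. But the section mentions dropout only once, after the 30, so this is conjecture.

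The article condenses a fuller protocol, and the source cited for the 25% rule is not at hand; the basis of the SD and correlation may be given there. That would not make a factor derived for +0.5 apply to deltas that share T3.

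**Conclusion.** The point holds: the sample size figure is wrong as written, and its power basis does not match the primary analysis. The 120 should be 98 to 100 on the stated inputs, a conservative error in isolation. The 25% factor should be 62.5% to 75% for the planned deltas. The claim that 30 completers suffice is unsupported. Of the four delta scenarios examined, only the most favourable one, a fully reversible score effect combined with decaying correlation, reaches 80%.

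The negative sign of the correlation follows from the shared T3 under either ordinary correlation pattern. The size of the shortfall rests on assumptions: two-sided testing, equal variances, adjacent-visit correlation of 0.5, the correlation pattern, and the scale of the 4 points.

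**What to change.** In 'Sample size calculation':

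1. Replace 120 by 98 to 100, or state what else the 120 contains.
2. State whether SD 7 and r = 0.50 refer to single scores or to delta scores, and on which scale the 4 points lie.
3. Restate the power at 30 completers for the delta analysis, using the SD and the negative correlation of the deltas, and bring the matching sentence in the Discussion into line.

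These are text changes and need no new data.

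As an option, the sponsor could make end-of-period scores (T3 versus T6, both already collected) the primary contrast. With a reversible 4-point effect, SD 7 and r = 0.50, 30 completers then give 86%. This is more than a wording change: it redefines the primary outcome in a trial already collecting data, so it needs an amendment, and it loses power if the effect persists after the switch.
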